### Ethical Considerations

This study involved human participants and is covered by French law 2012-300 of 5 March, 2012, known as the Jardé Law, as category 3 research involving the human person, which provides for the analysis of anonymized personal medical data previously collected during routine care. The sponsor and the person directing and supervising the research undertaken ensured that this research was carried out in accordance with the Jardé Law and the Declaration of Helsinki in its latest version.

The study protocol and related participant documents were reviewed and approved by the Comité de Protection des Personnes Sud-Est I (South-East Ethics Committee for the Protection of Persons; October 11, 2021), together with 3 substantial modifications along the course of the study carried out between November 1, 2021, and July 31, 2023. In addition, an ancillary qualitative study has been reviewed and approved by the Comité de Protection des Personnes Sud-Est I (South-East Ethics Committee for the Protection of Persons; May 9, 2022).

The controller and processor of data recorded during this research was the Centre Hospitalier de Cayenne (Cayenne Hospital Center) in accordance with the French Data Protection Act 78-17 of 6 January, 1978, amended by law 2004-801 of 6 August, 2004, and the European Union regulation (EU 2016/679), titled the General Data Protection Regulation.

This research falls within the scope of the Reference Methodology (MR-003). The Centre Hospitalier de Cayenne has signed an undertaking to comply with the Reference Methodology and has a certificate of compliance number 2215826 version 0 from November 20, 2019 (certificate renewed on December 21, 2021, under the number 2224668 version 0). A privacy impact assessment was carried out in accordance with MR-003.

This research was registered on ClinicalTrials.gov under the national clinical trial NCT05174234 and has ID-RCB (National Identifier generated by the French National Medicines Agency) number 2021-A02185-36.

Before the start of recruitment, agreements were signed with all participating centers as well as with relay points to facilitate recruitment by general practitioners, associations, and NGOs.

All those involved in the research have been trained on good clinical practice and the rules of confidentiality and medical secrecy. Before data collection, for all quantitative and qualitative aspects of the study, participants were provided with full information on the research, and a declaration of consent was completed. Finally, each participant was given an anonymized number, and all information was pseudonymized. As a thank you for the time spent in the interview (regardless of which part they participated in), participants received a compensation kit made of toiletry bag containing soap, body lotion, shampoo, condoms, masks, toothbrushes, and toothpaste.

Similarly, semistructured interviews could only be recorded after the participants provided their consent. Concerning viral sequences, after participants’ consent, the Pol gene sequence will be extracted from existing sequences, anonymized, and transferred securely to the partner laboratory at the Oswaldo Cruz Institute of the Oswaldo Cruz Foundation (Fiocruz) in Rio de Janeiro for analysis. No personal or identifying data will be transmitted to Fiocruz.

### Study Populations and Inclusion Criteria

For the quantitative epidemiological and biographical component, participants were included in 3 groups: a general population group, a group of people living with HIV, and a group of people living with HBV.

The inclusion criteria for all groups were as follows: being born in Haiti (regardless of current nationality), having been in French Guiana for >3 months, being aged between 18 and 60 years, and having no objection to participate in the study. For the group of people living with HIV, the inclusion criteria were as follows: living with HIV and having a diagnosis dating back >3 months (whatever their status with regard to hepatitis B and C), as well as being followed up on by one of the study’s partner physicians at the hospitals in Cayenne, Kourou, or Saint-Laurent-du-Maroni; in outpatient care; or by a partner association. For the group of people living with chronic hepatitis B, the inclusion criteria were living with a chronic HBV infection and having been diagnosed for >3 months (not coinfected with HIV), as well as being followed up on by one of the study’s partner physicians in the hospitals of Cayenne, Kourou, or Saint-Laurent-du-Maroni; in outpatient care; or by a partner NGO.

For the general Haitian population group (not known to live with HIV or HBV), the inclusion criteria were declaring that they were not infected with either HIV or HBV, being under the care of one of the study’s partner physicians, or being recruited in the public space of one of the cities targeted by the study (Cayenne, Matoury, Rémire-Montjoly, Macouria, Kourou, Montsinéry-Tonnegrande, Sinnamary, Maripasoula, Saint-Laurent-du-Maroni, or Mana). Exclusion criteria were being unable to answer the interviewer in French or Haitian Creole; being under guardianship, tutelage, or legal protection; and having already answered the study questionnaire.

For the exploratory qualitative sections focusing on health anthropology, mental health, and access to care, the inclusion criteria were tailored to each substudy and comprised the following professionals, including (1) health professionals, social workers, or members of local NGOs with experience working with migrants in French Guiana between 2021 and 2023 who agreed to participate in the study (the mental health and access to care substudies were conducted exclusively with health care professional), and (2) community members, including representatives of the Haitian community who met the inclusion criteria of being born in Haiti, regardless of their current nationality, residing in French Guiana for >3 months and who were aged >18 years and provided consent to participate in the study. For individuals living with HIV or HBV, the same criteria applied, with an additional requirement of being a diagnosed person living with HIV or HBV.

### Sample Size

The number of participants required was calculated to estimate the frequency of the main indicators (sexual behavior that exposes one to the risk of acquiring HIV, including inconsistent condom use with casual or commercial partners, having multiple sexual partners, engaging in concurrent partnerships, and exposure to sexual violence [20]) based on an expected percentage of 50% with a precision of 5% using the following formula:

In this formula, 

 is 1.96 for an agreed risk of 0.05, π is the frequency of the factor studied (in this case, 50% or 0.5), and Δ is the accuracy required (in this case, 5% or 0.05).

From estimates of a total of 384 participants per group, and to take into account incompleteness of data collection, the target was set at 400 people living with HIV and 400 people living with HBV. Considering a 1:2 ratio, 1600 participants were planned in the general population group to have sufficient power to carry out multivariate analyses on all study indicators and conduct analyses on subpopulations of interest, such as women, men, youth, people who arrived after 2015, people living in extreme poverty, and people who have used transactional sex.

Concerning the feasibility of including people living with HIV from Haiti, the number of patients actively being followed up on in Guiana’s hospitals was estimated at 889 in 2021. For the group of people living with HBV from Haiti, the cohort in 2021 was 250 people being actively followed up on in hospital departments. These data are largely underestimated as they do not take into account those who have been lost to follow-up. In terms of the general population, nearly 10% of the Guianese population is of Haitian origin. Thus, the recruitment objectives seem achievable in view of the study’s target population.

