### Participant Enrollment, Sampling Approaches, and Monitoring

For the quantitative aspects of the study, sampling of the Haitian population in French Guiana—little explored, partially hidden (living in informal settlements and without papers), and rapidly evolving—was carried out by combining several methods. Recruitment sites were chosen on a nonprobabilistic and reasoned basis. Locations were selected based on literature analysis, census data, knowledge of the peer community workers, knowledge of partner NGOs, and accessibility and safety. These criteria are listed in Figure 1. Finally, partner hospital departments, outpatient centers (health care access offices, French Red Cross prevention and health centers, and primary care centers), and general practitioners were identified. The hospital services selected were those that limited bias on morbidity (particularly chronic diseases). The medical departments selected for participant screening and enrollment were maternity, pediatrics, dermatology, and the emergency room. In view of the enrollment sites mentioned, an oversampling of women was expected and judged as acceptable.

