**Figure 1 figure1:**
[figure not shown]
Selection criteria for mapping and choosing locations for recruitment for the Parcours d’Haïti study between 2021 and 2023. NGO: nongovernmental organization.

At the recruitment sites, random recruitment was carried out—all people meeting the inclusion criteria were invited to take part in the study. Recruitment was halted once we reached a reasonable number of participants from a statistical power perspective and representativity of the study populations.

To improve the representativeness of the sample, additional recruitment using the snowball method was planned among eligible health and social care professionals and resource persons. Each volunteer participant received 8 cards with an alphanumeric code to be distributed to eligible people within their circle. Those who received a card and wished to participate were able to contact the peer investigators to schedule an interview according to their availability. The entire protocol was explained to them, and they were able to ask any questions they wished before agreeing to take part. This method was used to improve the quality of the sample and minimize selection bias in terms of care and social support as well as insecurity.

For the qualitative components, the samples were chosen based on predefined inclusion criteria, developed previously, to represent the different profiles of stakeholders and individuals. Sampling was stopped for each component when data saturation in the answers was reached.

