#### Statistical Analysis of Quantitative and Biographical Data

With regard to the statistical analysis of quantitative information, the major indicators will be described using percentages as well as means or medians with their SDs or IQRs depending on their distribution. Analytical work will be carried out with a biographical and social epidemiology approach using the tools of epidemiological analysis to study the associations between behaviors and health indicators and social determinants. Factors associated with biographical key indicators will be analyzed year after year using discrete-time logistic regression models that take into account time and the values of indicators collected in the biographical grid year after year [31]. Factors associated with indicators collected at the time of the study will be analyzed using Poisson regression with robust variance. The Stata software (StataCorp) will be used to conduct the analyses.

An analysis of the participants’ support and care structures will be carried out based on specific questions that will be analyzed through clustering and a bipartite network approach using methods derived from graph theory. These analyses will provide a better understanding of the levers and care itineraries that can be developed. The R software will be used for these analyses (*tidyverse* and *tidygraph* packages).

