### Limitations

The study methodology has a number of limitations. First, the target population is hidden, most of them undocumented, and the situation (particularly in informal settlements) is rapidly changing. As information on their distribution was incomplete, it was difficult to assess the representativeness of this population in the territory in the absence of up-to-date comparative data. The recruitment sites were selected on a nonprobabilistic and reasoned basis, so selection bias cannot be excluded.

One of the limitations of this study is the strong stigma attached to the Haitian community, particularly the association between the terms “Haiti” and “HIV,” which has a historically negative connotation. This association could reinforce the stigma already attached to this population and limit acceptability.

The recruitment targets for the hepatitis B and HIV groups were ambitious, and the active referral files did not take into account patients lost to follow-up or the growing proportion of patients followed up on in the city (which is difficult to reach).

With regard to the inclusion of participants living with hepatitis B, the follow-up departments for these patients were late in signing up as this study group was added at a later stage, limiting the time available for recruitment.

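### The ±5% precision is a simple-random-sampling figure with no design effect, although recruitment ran through purposively chosen sites, clinics and card referral; the 400-person groups have almost no room for clustering

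*Protocol article*

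**What the plan says.** **Size.** The Sample Size section sets the number per group "based on an expected percentage of 50% with a precision of 5% using the following formula". The normal deviate "is 1.96 for an agreed risk of 0.05". The result is 384 per group. The HIV and HBV targets are raised to 400 each to cover incomplete data. The general population target of 1600 is justified by a 1:2 ratio and by power for multivariate and subgroup analyses. No allowance for clustering is mentioned.

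**Sampling.** Under Participant Enrollment, Sampling Approaches, and Monitoring: "Recruitment sites were chosen on a nonprobabilistic and reasoned basis". Next: "At the recruitment sites, random recruitment was carried out", which the same sentence explains as inviting everyone eligible at those sites. Snowball recruitment was added: "Each volunteer participant received 8 cards with an alphanumeric code to be distributed to eligible people within their circle". On stopping: "Recruitment was halted once we reached a reasonable number of participants from a statistical power perspective and representativity of the study populations". Study Populations and Inclusion Criteria draws the HIV and HBV groups from patients followed by partner physicians at three hospitals, in outpatient care, or by partner associations or NGOs.

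**Analysis.** "Factors associated with indicators collected at the time of the study will be analyzed using Poisson regression with robust variance". Discrete-time logistic models are planned for the biographical indicators, with no variance estimator given. No cluster unit is named for either.

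**Limitations.** Selection bias from nonprobabilistic sites is acknowledged, and "it was difficult to assess the representativeness of this population in the territory in the absence of up-to-date comparative data". Loss of precision is not mentioned.

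**The concern.** The formula treats the participants in a group as independent draws. People met at the same site, followed by the same service or recruited through the same acquaintance may resemble each other, both in sexual behaviour and in the living conditions whose association with it belongs to the main objective. If so, 400 people carry the information of fewer than 400 independent ones.

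Two things are at stake. First, the precision claimed for the primary frequency may not be reached in the groups sized to the bare minimum. Second, if the analysis ignores the correlation, confidence intervals would be too narrow and p-values for associations with living conditions too small. Robust variance for a binary outcome in a Poisson model repairs the wrong variance function. It does not handle correlation between participants unless a cluster is specified.

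The wording adds to this. Inviting everyone eligible at hand-picked sites is not random selection, and stopping partly on representativeness sits badly with the later statement that representativeness was hard to assess.

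**Working it through.** **Inputs from the Sample Size section:** z = 1.96, π = 0.5, Δ = 0.05; targets 400 (HIV), 400 (HBV), 1600 (general population); 889 followed HIV patients.

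**Inputs assumed:** the design effect (DEFF), cluster size m and intraclass correlation (ICC). The documents give none of these, nor the snowball share, so ranges are shown.

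**1. Reproduce the plan's figure.** The formula itself is not shown in the text, but its listed terms identify it:

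n = z²·π(1−π)/Δ² = 1.96² × 0.25 / 0.05² = 384.16.

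This matches 384, so the figure is a simple-random-sampling one with DEFF = 1.

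**2. Room left for clustering.** The largest DEFF that keeps ±5 points is n/384.16.

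- n = 400: 400/384.16 = 1.04. This slack is already assigned to incomplete data; with 384 complete records there is none.
- n = 1600: 1600/384.16 = 4.16.

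**3. Half-width and required size.** Half-width = 1.96·√(DEFF × 0.25/n); n needed for ±5 points = 384.16 × DEFF, rounded up.

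| Assumed DEFF | Half-width, n = 400 | Half-width, n = 1600 | n needed for ±5 points |
|---|---|---|---|
| 1 | 4.9 | 2.45 | 385 |
| 1.2 | 5.4 | 2.7 | 461 |
| 1.5 | 6.0 | 3.0 | 577 |
| 2 | 6.9 | 3.5 | 769 |
| 3 | 8.5 | 4.2 | 1153 |
| 4 | 9.8 | 4.9 | 1537 |

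**4. What such design effects require.** DEFF = 1 + (m − 1)·ICC.

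- m = 20, ICC = 0.02: DEFF = 1.38; ±5.8 points at 400, ±2.9 at 1600.
- m = 20, ICC = 0.05: DEFF = 1.95; ±6.8 points at 400, ±3.4 at 1600.
- m = 40, ICC = 0.10: DEFF = 4.9; ±5.4 points at 1600, an example where the large group also misses.
- With m = 20, the 400-person limit is reached at ICC = 0.0412/19 = 0.002.

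**5. Coverage if clustering is ignored.** Actual coverage of a nominal 95% interval = 2Φ(1.96/√DEFF) − 1: about 93% at DEFF 1.2, 89% at 1.5 and 83% at 2.

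**6. Subgroups.** A 400-person subgroup of the general population group has the same limit of 1.04 as the HIV group. A subgroup spread over many sites has fewer members per site, so its DEFF may be smaller than that of the whole group.

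**7. Finite population check.** If inference were restricted to the 889 followed HIV patients, the variance is multiplied by (889 − 400)/888 = 0.551. The half-width at 400 becomes 4.9 × √0.551 = 3.6 points, and ±5 points holds up to DEFF = (5/3.64)² = 1.89.

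**The case against.** **Missed precision is not shown for every group.** A reader might infer that the stated precision fails throughout. The documents do not support that: the 1600-person group, where public-space recruitment applies, meets ±5 points overall at design effects of 2 and 3. This stands.

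**For the 400-person groups the shortfall is possible, not demonstrated.** These patients come from partner services. If those services cover nearly all followed patients, site acts more like a stratum than a sampled cluster, and for inference limited to the 889 HIV patients the finite population correction leaves room up to DEFF 1.89. That is fair as far as it goes. But the article itself says such counts omit patients lost to follow-up, and the sample-size formula claims no such restriction. For HBV the correction cannot be used, because the target of 400 exceeds the 250 people in the listed cohort.

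**The planned standard errors may be adequate.** A reader might infer that the analysis assumes simple random sampling. The article does not say so: it does not specify the form of robust variance, and the cluster unit may be given in a full protocol or analysis plan that is not shown. The supportable statement is conditional: intervals would be too narrow if clustering is ignored.

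**The inputs are assumed, and selection bias may matter more.** Both are true. Snowballing was an addition and may have contributed few participants. Staff departments such as maternity or emergency care may see people with quite different living conditions. Neither a design effect nor clustered variance removes selection bias, which Limitations already admits.

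**Random recruitment is explained in the same sentence,** and the nonprobabilistic choice of sites is disclosed twice. The reader is therefore not misled for long, but the term is still wrong.

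**Conclusion.** The point holds in a limited form. The Sample Size section uses a simple-random-sampling formula, while the enrolment section describes purposive sites, partner services and referral cards. This mismatch lies in the article itself and does not depend on an unseen plan.

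The consequence falls mainly on the HIV and HBV groups. Their margin is a design effect of 1.04, and that margin is already spent on incomplete data; assumed design effects of 1.5 to 3 give half-widths of 6.0 to 8.5 points in place of 5. The general population group is safe overall up to 4.16, with less room in its subgroups. The true design effect cannot be computed from the documents and may differ between groups.

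Too-narrow intervals and too-small p-values follow only if the analysis leaves site and chain correlation out. The article names no cluster unit, but it does not rule one out. The description of recruitment as random is incorrect whatever the design effect. The stopping reason based on representativeness is not backed by any check the article could make.

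**What to change.** The Analysis Plan section says analyses had not begun at submission, so these changes could be made before results are seen.

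1. **Precision.** Label ±5% as a planning figure under simple random sampling. Add a short table of half-widths over a range of design effects, mainly for the 400-person groups and the named subgroups.
2. **Variance.** Cluster on recruitment site for percentages, Poisson models and discrete-time models. Assign snowball recruits to their referral chain where the card code was recorded and linked to the recruiter; the article says the cards were coded but not that the link was kept. Because participants are nested in sites or chains, this also covers the repeated years from one person in the discrete-time models.
3. **Few clusters.** Ordinary cluster-robust variance is unreliable with a handful of hospitals. There, use a small-sample correction or site fixed effects in the models, noting that fixed effects estimate within-site associations.
4. **Sensitivity.** Repeat the main estimates without snowball recruits.
5. **Wording.** Replace the term random recruitment by a statement that all eligible people at purposively chosen sites were invited. The stopping reason reports a past event and cannot be withdrawn; add beside it that representativeness could not be verified.

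**Cost:** modest programming, a check of whether site and card code are in the database, wider intervals and a less favourable stated precision. None of this cures selection bias, and the report should say so.

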### Participant Enrollment, Sampling Approaches, and Monitoring

For the quantitative aspects of the study, sampling of the Haitian population in French Guiana—little explored, partially hidden (living in informal settlements and without papers), and rapidly evolving—was carried out by combining several methods. Recruitment sites were chosen on a nonprobabilistic and reasoned basis. Locations were selected based on literature analysis, census data, knowledge of the peer community workers, knowledge of partner NGOs, and accessibility and safety. These criteria are listed in Figure 1. Finally, partner hospital departments, outpatient centers (health care access offices, French Red Cross prevention and health centers, and primary care centers), and general practitioners were identified. The hospital services selected were those that limited bias on morbidity (particularly chronic diseases). The medical departments selected for participant screening and enrollment were maternity, pediatrics, dermatology, and the emergency room. In view of the enrollment sites mentioned, an oversampling of women was expected and judged as acceptable.

